##### Aim 2 Power Analysis

We used the NCSS PASS [76] module for three-level multilevel models with randomization at the cluster level to compute the minimum detectable effect size estimates for hypotheses H2a-H2e. We assumed power = 0.80, α = 0.05, and 2 post-baseline repeated assessments from *N* = 400 enrolled providers from 40 health facilities (*N* = 320 following 20% conservatively assumed attrition based on pilot data and our planned approach to reduce attrition) [52]. We conservatively assumed ICC = 0.15 based on our preliminary data [46, 67, 77]. Since the within-provider correlations are unknown, we varied them from *r* = .20 (small) to *r* = .80 (large). We computed the minimum detectable standardized mean difference *d* using the same inputs as listed above, yielding *d* = 0.40 to 0.44, which are between thresholds for small (0.20) and medium (0.50) standardized effects, suggesting the sufficient power to detect small to medium effects [78].

##### Aim 3

Improvements in PCMC are hypothesized to impact timely and appropriate care provision, care engagement, future health-seeking, and the physical and psychosocial health of women and their babies who receive care from those facilities, all of which positively influence maternal and neonatal outcomes. Recognizing that these distal outcomes are influenced by broader contextual factors and take longer to change, we propose an exploratory third aim to assess the impact of CPIPE on these outcomes during the study period and whether they are mediated by changes in PCMC. Given the exploratory nature of this aim, initial analyses will be descriptive, with frequency tables for all distal outcomes and measures of central tendency and variability for continuous distal variables at 6 and 12 months for intervention and control sites.

While facility data will be limited to *N* = 40 clinics, inferential analyses will be performed with *N* = 2000 women on distal outcomes. We focus on the key outcome of receipt of timely post-natal care. We hypothesize that among mothers giving birth in the study facilities, mothers who received care in the *CPIPE* intervention group will be more likely to receive postnatal care within 48 h than mothers in the control group at 6 months (H3a) and 12 months (H3b) after baseline. To test H3a and H3b, we will fit two-level generalized linear mixed models (GLMM) to the binary timely postnatal care variable collected at 6 months and at 12 months. Each model will include a fixed effect for study arm and random intercepts for facilities for clustering of women within health facilities. Because we will compare *CPIPE* to control at 6 months and at 12 months, α will be set at.05/2 = 0.025 for each comparison. We will use the same GLMM approach to test the effects of *CPIPE* on other distal outcomes. Additional secondary exploratory analyses for Aim 3 will explore whether the PCMC scores mediate the relationship between *CPIPE* intervention exposure and receipt of timely post-natal care. As in specific Aim 2, we will perform mediation analyses using SEM and causal mediation methods [79]. Sex as a Biological Variable is not applicable because all care recipients will be biological females.

##### Aim 3 Power Analysis

We used a similar approach as for Aim1 to compute the minimum detectable effect size estimates for hypotheses H3a-H3b, assuming a broad range of 24–81% of women receiving timely post-natal care and ICC = 0.039 at the facility level based on our previous data [20, 77]. Minimum detectable raw proportion differences were 8.3–10.7%, which correspond to small to medium effects [78].

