### Randomization

Randomizing individual providers is not ideal because of a high potential for contamination within facilities and goal of changing facility culture. A cluster RCT design allows us to address threats to internal validity and account for natural clustering of providers within facilities [57]. Forty facilities will be randomized to intervention (*N* = 20) and control (*N* = 20), with arms stratified by country(10 intervention and 10 control facilities in each country). To reduce the risk of contamination due to interaction of providers within the same sub-counties and districts, randomization will be at the sub-county/district level such that control and intervention facilities are not in the same sub-county/district. The facility randomization will be done by a statistician not directly involved in the study. The intervention group will receive all strategies of the *CPIPE* intervention strategies over a period of 6 months after the baseline data collection. At the end of the 6-month implementation, we will collect midline data. Facilities will then be encouraged to continue with the intervention activities without involvement of the study for an additional 6 months, with final data collection at 12 months (endline). The control group will not receive the CPIPE intervention during the 12-month data collection period but will maintain their usual facility level activities. We plan to implement the intervention in the control sites after the endline data collection (assuming preliminary effectiveness). The protocol complies with the standard protocol items for cluster randomized trials. The study design, outcomes, and participant flow are summarized in Figs. 2 and 3.

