##### Aim 1 Power Analysis:

We used the NCSS PASS [76] module for a two-level multilevel model with a continuous outcome and randomization at the cluster (i.e., health facility) level to compute the minimum detectable effect size estimates for hypotheses H1a-H1b. We assumed power of 0.80, α = 0.025 per comparison, and *N* = 2000 women from 40 facilities. We further assumed ICC = 0.16 based on our previous data [20, 77]. The minimum detectable standardized mean difference was *d* = 0.41, which is between small and medium effect size, suggesting the proposed primary analyses have sufficient power to detect small to medium effects [78].

##### Aim 2

We anticipate that the intervention will positively impact the intermediate outcomes in our conceptual model (Fig. 1), leading to an improvement in PCMC. We thus hypothesize that, following *CPIPE* exposure, intervention providers will have, higher mean scores on provider knowledge (H2a); self-efficacy (H2b); enabling environment (H2c); behavior (H2d), and lower mean scores on work-related psychological effects (stress, burnout, and bias) (H2e) relative to control providers. To test these hypotheses, we will fit three-level LMMs to each intermediate outcome, with fixed effects for study arm, time, and their interaction, random intercepts for facility ID to account for clustering of providers within health facilities, and random intercepts, random slopes, and their covariance for person ID to account for clustering of repeated measurements within providers. We will perform time-averaged comparisons of repeatedly measured post-baseline observations of the key intermediate outcomes across study arms to examine *CPIPE* intervention effects.

In secondary exploratory analyses, we will investigate whether the intermediate outcomes measured for providers at 6 months mediate the relationship between *CPIPE* intervention assignment and PCMC at 12 months. These analyses will be conducted using principles of structural equation modeling (SEM) and causal mediation methods [1]. We will explore whether *sex as a biological variable* differentially affects intervention effects on the provider-level primary analyses by adding a sex main effect and a sex-by-*CPIPE* assignment interaction term to the LMM models. Sex as a biological variable is not applicable to the mediation analyses due to the outcome applying to women only.

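### The Aim 3 minimum detectable difference of 8.3–10.7% holds only at the two ends of the assumed 24–81% range; inside it the figure rises to 11.7 points

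*Protocol article*

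**What the plan says.** The Aim 3 Power Analysis covers hypotheses H3a and H3b, on postnatal care within 48 hours at 6 and at 12 months. It describes its method as follows: "We used a similar approach as for Aim1 to compute the minimum detectable effect size estimates for hypotheses H3a-H3b". It proceeds by "assuming a broad range of 24–81% of women receiving timely post-natal care", takes a facility-level ICC of 0.039, and concludes: "Minimum detectable raw proportion differences were 8.3–10.7" per cent. It calls these small to medium effects. It does not say that only particular rates within the range were evaluated.

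The remaining inputs come from elsewhere in the article. The Aim 3 analysis text fixes the significance level: "α will be set at.05/2 = 0.025 for each comparison". The Aim 1 Power Analysis supplies the rest: "We assumed power of 0.80, α = 0.025 per comparison", with "2000 women from 40 facilities". The Randomization section gives equal allocation: "10 intervention and 10 control facilities in each country".

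**The concern.** A range of detectable differences printed next to a range of assumed rates reads as covering those rates, with the larger figure as the worst case. For a proportion the worst case is not at an end of the range when the range spans 50%, because the variance p(1 − p) peaks there. If the calculation was run only at 24% and 81%, the upper limit is too small for rates in between.

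Timely postnatal care is the outcome that Aim 3 singles out for formal testing, with its own split of alpha. A reader interpreting a null result would take it that a 10.7-point difference had at least an 80% chance of being detected whatever the control rate. For a mid-range control rate that chance is lower.

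**Working it through.** **Inputs**

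- Women per time point: 2000 in 40 facilities, so 50 per facility and 1000 per arm (Aim 1 Power Analysis; Randomization).
- ICC 0.039 (Aim 3 Power Analysis).
- Alpha 0.025 per comparison (Aim 3). Power 0.80 (Aim 1, carried over by the reference to a similar approach).
- Direction: an increase over control (H3a, H3b).
- Sidedness: not stated. Two-sided is assumed, so z = 2.241 for alpha and 0.842 for power.

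**Check of the method on Aim 1.** With ICC 0.16 the design effect is 1 + 49 × 0.16 = 8.84, and d = (2.241 + 0.842) × √(2 × 8.84/1000) = 0.410. The article prints 0.41, so a two-sided 0.025 test with this design effect matches.

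**Aim 3 set-up.** Design effect = 1 + 49 × 0.039 = 2.911. Effective sample size per arm n = 1000/2.911 = 343.5. For control rate p1, with p2 = p1 + d and p̄ the mean of the two, solve

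d = 2.241 × √(2p̄(1 − p̄)/n) + 0.842 × √((p1(1 − p1) + p2(1 − p2))/n).

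**Reproducing the printed limits**

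- p1 = 24%: d = 0.0779 + 0.0290 = 0.1069, against 10.7 printed.
- p1 = 81%: d = 0.0608 + 0.0227 = 0.0834 (parts rounded), against 8.3 printed.

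**Across the whole range**

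| Control rate | Minimum detectable difference (points) | Power for a 10.7-point difference |
|---|---|---|
| 24% | 10.7 | 80% |
| 30% | 11.2 | 76% |
| 40% | 11.7 | 72% |
| 44–45% | 11.7 (11.74, maximum) | 71% |
| 50% | 11.7 | 72% |
| 60% | 11.2 | 76% |
| 65% | 10.7 | 80% |
| 70% | 10.2 | 85% |
| 81% | 8.3 | 97% |

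In steps of 0.1 point, the result exceeds 10.7 for control rates from 24.1% to 65.2%, which is 72% of the width of the range. Counting only values that would no longer round to 10.7 (above 10.75), the interval is 24.6% to 64.7%, or 70%.

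**Power at the peak.** At p1 = 45% and p2 = 55.7%, the pooled standard error is 0.03815 and the unpooled one 0.03793. Then (0.107 − 2.241 × 0.03815)/0.03793 = 0.567, and power is Φ(0.567) = 71%. With the same design effect, 80% power for 10.7 points at a control rate of 44% would need about 1205 women per arm, against 1000.

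**Sensitivity to the formula.** At two-sided 0.025 the peak is 11.7 to 11.8 points with pooled, unpooled, arcsine or control-rate-only variance, and 12.1 to 12.2 with a t reference on 38 degrees of freedom. None keeps the maximum at 10.7.

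**The case against.** The strongest reply is that 24% and 81% may be two scenarios drawn from earlier data, with 10.7 and 8.3 as the results at each. On that reading both numbers are correct. The article, however, speaks of a broad range and does not label the results as end-point values. That only the ends were evaluated is an inference from the numerical match, not something the article says.

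Second, the Aim 3 paragraph restates neither power, alpha nor sidedness. At two-sided 0.05 (equivalently one-sided 0.025) the pooled calculation peaks at 10.67 points, which also rounds to 10.7. That setting gives 7.7 points at 81%, not 8.3, and two-sided 0.05 contradicts the alpha stated for Aim 3. With control-rate variance it comes closer, 8.4 at 81% and a peak of 10.7 at 50%, but still misses the lower limit. Taking the effect as a decrease gives 9.3 at 24% and 10.0 at 81%, which fits neither limit. The two-sided 0.025 reading fits best.

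Third, the consequences are small, and this stands. The excess is at most about 1 point, and close to either edge of the affected interval it is only about 0.1 (10.8 points at control rates of 25% and 64%). On the arcsine scale the detectable effect is nearly constant, 0.235 to 0.237 across the range, so the small-to-medium description is as true at 11.7 points as at 10.7. The aim is expressly exploratory.

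A reader might infer more: that power is overstated for most rates likely to occur. The documents do not support that. They give no weighting of rates within 24–81%, so the 70% describes the width of the interval and not the chance that the true rate falls there.

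**Conclusion.** Wrong as written, of minor severity. The upper limit printed for the assumed range should be 11.7 points rather than 10.7; the lower limit of 8.3 is right. The largest shortfall in power for a 10.7-point difference is about 8.5 percentage points (71.5% against 80%).

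This rests on a two-sided test, the normal approximation with 50 women in each facility, and 24–81% read as control rates with an increase under intervention. Those choices reproduce both printed limits to the decimal given. The primary outcome, the alpha allocation and the planned sample are untouched.

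**What to change.** In the Aim 3 Power Analysis, replace the printed range with: 8.3–11.7 percentage points over control rates of 24–81% (maximum near 45%). State there that the test is two-sided at 0.025 with power 0.80, so that the figure can be reproduced. If the two printed values were meant only for control rates of 24% and 81%, label them as such and add the mid-range maximum. The cost is one corrected number and a short clause; no design element or analysis changes.

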### Qualitative analysis

The sample size for the qualitative study is informed by guidelines to achieve data saturation [80, 81] and a desire to purposively sample from all the study facilities. We will record interviews and transcribe audio recordings into English, translating if interviews are conducted in local languages. Transcripts will be coded and analyzed in Dedoose software utilizing collaboratively developed coding frameworks and group approaches qualitative analyses, guided by the thematic analysis approach described by Braun and Clark [82]. To capitalize on the mixed-methods design, findings from the qualitative and quantitative data collection and analyses will be integrated at the interpretation and discussion stages. All team members who collect the data will be included in the analyses to strengthen the validity of the findings.

### Cost-effectiveness analysis

We will also assess the cost-effectiveness of CPIPE on PCMC.

#### Costing

We will use standard micro-costing techniques and include a full costing approach, which requires the estimation of both recurrent and capital costs related to the intervention. The recurrent costs will include the cost of materials used within a year, which will include the cost of personnel salaries/allowances, medical consumables, training and meetings, travels, office supplies, and overhead/administrative costs related to the intervention development and delivery. The capital costs will be the inputs or resources that usually last for more than one year, which include items such as facility/office space, equipment, and vehicles/motorbike/bicycle costs. Research costs will be excluded. Capital costs will be annualized using a discount rate of 3% and the useful life of the capital items. The total economic costs of the intervention will be estimated and then categorized into pre-intervention deployment costs, intervention implementation costs, and indirect costs.

#### Effectiveness

The effectiveness outcome will be the PCMC scores measured for women at 6 months and at 12 months.

#### Cost-effectiveness analysis

The incremental cost-effectiveness ratio (ICER) will be used in the estimation of the cost-effectiveness of the CPIPE intervention. The ICER is the incremental cost per incremental benefit due to in CPIPE intervention. A budget impact analysis will be carried out to determine the impact of the intervention implementation and scale-up on the government budget.

### Process evaluation

We will conduct a process evaluation to assess implementation and intervention fidelity including adherence, exposure, quality of delivery, competence, participant responsiveness, and program differentiation [58, 59]. We will use mixed-methods approaches for this purpose, guided by Proctor’s framework [83, 84]. A fidelity monitoring tool with structured and open-ended questions will be used to document all implementation activities, noting details such as the timing of activities, participants, facilitators, the content of the activity, and what went well and what did not go well. We will also document ongoing activities at each site to identify activities that might affect the outcomes of the trial.

### Timeline

The CPIPE trial will be completed over a 5-year period. We will use the first 6 months for study preparation activities, including finalizing the protocol and data collection tools, updating the curriculum with lessons learned from the pilot, and obtaining ethical and other regulatory approvals at UCSF and all sites. We will implement the intervention in 2 blocks in each country, with 10 facilities (5 intervention and 5 control) in each block. Baseline data collection for the first block will start in Y1Q3, followed by intervention implementation, midline, and endline over a period of about one and a half years. Baseline and intervention activities in the next block will start in about Y2 following the same approach in the next year. In year 3 we will offer the intervention to the control groups. Data collection across all sites is anticipated to be completed in Y4. Data cleaning, quality assessment, and preliminary analysis will occur as data are being collected. In year 5, we will continue with data analysis and preparation of manuscripts and presentations, with dissemination in Ghana, Kenya and globally.

### Safety monitoring

The study has been approved by the study teams’ institutional review boards (IRBs) in the United States, Ghana, and Kenya (see details in ethics approval and consent to participate section). Any protocol amendments will be reported to all the relevant IRBs. The studies’ sponsors and IRBs agree that the activities in this protocol represent minimal risk. Thus, a data monitoring committee is not required. The study team will, however, monitor activities and data per our approved data safety monitoring plan. The research team will be trained to recognize and immediately report any adverse events to ensure the safety of participants. The PI, in consultation with the research team, will be responsible for evaluating any adverse events and responding appropriately. Participant confidentiality will be protected during data collection by conducting interviews in private locations. Participants will be assigned a unique identifier, and all data entered in the study database will only utilize this identifier. All study data will be stored in secured and encrypted servers, which only authorized study personnel can access using password-protected devices. Given the study has minimal risk, no interim analysis is planned to inform study termination, and no formal auditing is planned beyond ongoing process evaluation activities.

## Discussion

The proposed intervention will be among the first, if not the first, rigorously designed and evaluated interventions to improve PCMC that address key drivers of poor PCMC, including provider stress and bias. The results will significantly advance the evidence base for interventions to improve PCMC and contribute to equity in maternal and neonatal health. A limitation of the *CPIPE* intervention is the inability to address structural factors such as shortage of health workers and supplies that affect provider stress and PCMC. These are important but beyond the scope of one intervention. This intervention is intended to help providers cope and provide better care amid the structural challenges. However, by collecting data on these issues and engaging leadership, we will provide the data and platform to prioritize and address structural challenges and inform policy decisions at the county, regional, and national levels. Additionally, the problem-solving strategies identified during the intervention period may help address and advocate for some of these structural challenges.

While recruitment and retention of providers may be a challenge, we will use lessons from the pilot studies, where we have achieved our target sample sizes, even during the COVID-19 pandemic. We have longstanding relationships and collaborations with health systems leaders in the study counties/regions, which will be critical to our success. In addition, our prior work has indicated both high need and interest in this intervention in the study areas [20, 52]. To reduce attrition, we will work with the county leadership to minimize the transfer of providers during the study period where possible. To mitigate challenges with the recruitment of women, we will utilize lessons from our prior studies such as working with community health volunteers and providing small incentives to both the women and volunteers who facilitate their recruitment. Other potential challenges include contamination from other related interventions in the study areas. As part of our process monitoring, we will document ongoing activities at each site to help explain unexpected findings.

Integrated provider-targeted interventions that give providers the opportunity to learn, practice, and reflect on their own as well as the patient experience with attention to the needs of the most vulnerable, and which create an enabling environment for behavior change, have the potential to improve both the providers and women’s maternal experiences. Incorporating such interventions into in-service professional development programs will help advance global efforts to promote PCMC. If the intervention is proven to be effective, it will be disseminated to the Kenyan and Ghana Ministries of Health, as well as non-government stakeholders. We anticipate expanding this work elsewhere in SSA and working to develop guidelines for scaling similar interventions. This research will address a major gap in efforts to improve MCH outcomes and achieve equitable maternal and neonatal health. The results of the trial will be disseminated through presentations, peer-reviewed publications, policy briefs, and other dissemination formats.

## Data Availability

No datasets were generated or analysed during the current study.
